## Abstract

**Background:**

Several studies have reported the following as determining factors for the adoption of healthy lifestyles among undergraduate students: gender, socioeconomic level, prior lifestyles, environment, parental lifestyles and health status, career choice, and healthy support networks. However, these factors are influenced by students’ knowledge about healthy lifestyles.

**Methods/design:**

We will carry out a randomized trial in a sample of 280 new undergraduate students at the National Autonomous University of Mexico’s Faculty of Higher Studies-Zaragoza (FES-Zaragoza, UNAM). There will be an experimental group (n = 140), comprising 20 students from each of the seven university departments (careers); these students will receive training as university student health promoters through an e-learning course. This course will allow the topics necessary for such promoters to be reviewed. There will be a control group (n = 140), comprising 20 students from each of the seven departments (careers); these students will not undergo the training. Later, the students who comply satisfactorily with the e-learning course will replicate the course to 10 of their classmates. A healthy-lifestyle questionnaire will be given to all the participants, and the parameters established in the self-care card will be recorded before and after the training. The study variables are as follows: (i) independent variable—compliance with the e-learning course; (ii) dependent variables—lifestyles changes prior to the educative intervention (including healthy eating, physical activity, and addiction prevention) and parameters related to health status established in self-care (including weight, body mass index, waist circumference, and hip circumference). Data will be analyzed using Student’s *t* test and logistic regression analysis odds ratios with 95% confidence intervals. The analysis of the open answers will be carried out with ATLAS. ti 5.5 software.

**Discussion:**

Health promotion among university students should incorporate options that are feasible for and attractive to students. Thus, as proposed in the present protocol, e-learning courses offer excellent possibilities because they allow students to program their learning in their available time without affecting their academic studies.

**Trial registration:**

http://ISRCTN77787889

## Background

Integrative professional development encompasses ethical, affective, humanistic, esthetic, sociopolitical, and health-care dimensions in addition to theoretical, disciplinary knowledge and obtaining technical competencies [1-3]. In this regard, it has been demonstrated that there is a relationship between university students’ health status and academic performance—hence; implementing health-promotion programs during their academic development is important [4]. However, it has been observed that many university students do not attach importance to their health care and even report their health status as being good or very good despite their lifestyles being unhealthy [5].

Self-care is understood as an individual’s reasoned behavior; it has a theoretical basis that allows the individual to act and decide on the prevention, diagnosis, and treatment of disease as well as maintaining their health and enjoying maximal quality of life (QOL) according to their sociocultural context. It constitutes an operative strategy of empowerment for maintaining health that is fundamental to developing all dimensions of a future professional’s integrative development [6,7].

QOL and health status differ even among countries in the same region, as has been demonstrated in European university students. In this respect, among British university students, it was observed that 70% of them did not comply with recommended physical activity, 66% consumed less than the recommended amount of fruits and vegetables, and 56% consumed alcohol at least once a week [8]. Likewise, there are great gender differences: women report less smoking, lower alcohol intake, and lower use of illegal substances, although they consume more fruits and vegetables. Males have a higher level of physical activity, consume fewer sweets, and have more restorative sleep [9]. It has also been reported that females have a lower frequency of psychological problems [10]. On the other hand, in a study carried out on Spanish students, it was found that 68.4% of males and 48.4% of females engaged in physical activity according to recommended levels. Similarly, students who undertook physical activity consumed more fruits and vegetables and smoked less than those who did not do any physical activity. In the same study, it was found that sedentary males devoted more time to using a computer, and sedentary females devoted more time to watching television [11]. The academic antecedents and lifestyles of the students’ parents were determining factors in physical exercise among the young people. The results of that studies suggest that healthy lifestyles are linked to behavior of social nets conformed, which supports the notion that health is transmittable.

Among Greek university students, it was observed that although females reported less physical exercise than males, their nutrition was better and their rates of overweight and obesity were lower than those of males. Likewise, medical students reported a lower frequency of alcohol consumption, although there were no differences with respect to eating habits compared with other university majors [12].

With respect to alcohol consumption, better habits have been observed in female Swedish university students than in males; however, females reported greater psychological stress, and males showed a higher percentage of overweight and obesity linked to refuse of advice on nutrition and worse healthy lifestyles [13]. On the other hand, Bulgarian students reported consuming sweets, cakes, and snacks more frequently, whereas Polish students consumed fewer fruits and vegetables. In general, males consumed more snacks than females (except in Bulgaria), and students who lived in home with their parents consumed more fruits and vegetables than those who lived alone or with friends [14].

On the other hand, in a study carried out among Lebanese university students, 37% overweight and 12.5% obesity was observed in males; 13.6% overweight and 3.2% obesity was recorded in females. In contrast, 6.4% of females and 1% of males were underweight [15]. Likewise, 22.9% overweight or obesity was recorded among Canadian university students; females were more concerned about their body weight than males, although their lifestyles and health status did not show significant differences [16].

In general, it has been demonstrated that women are more concerned about their body weight than men. Women exhibit better health habits, although they report more psychological problems [12-17].

One relevant aspect to student lifestyles is the changes observed with time at university, particularly if the students’ studies involve health, as in the case of medical students. In this respect, the 15% of the London students were non-drinkers, among those who drank, 48% of the men and 38% of the women exceeded sensible weekly limits of alcohol consumption [18]. Also it has been observed that the consumption of alcohol diminished with their time at university [19]. This supports the proposal of implementing a university health-promotion program so that all students—irrespective of their majors—possess adequate knowledge about adopting healthy lifestyles.

The present study will be carried out at the National Autonomous University of Mexico’s Faculty of Higher Studies-Zaragoza (FES-Zaragoza, UNAM). This university campus is a UNAM multidisciplinary faculty and was founded in 1976; currently, it offers undergraduate studies in the following seven academic majors: (i) medical surgery (*n* = 1,434); (ii) dental surgery (*n* = 1,672); (iii) nursing (*n* = 1,357); (iv) psychology (*n* = 2605); (v) biology (*n =* 1398); (vi) biological/pharmacological chemistry (*n* = 1,652); and (vii) chemical engineering (*n* = 1039). There are in addition some postgraduate courses.

In some unpublished studies conducted on students at FES- Zaragoza, UNAM, it was found that 40% of students were either overweight or obese as a consequence of unhealthy lifestyles. Surprisingly, students undertaking careers in the health sciences (medicine, nursing, odontology, and psychology) had a higher percentage of overweight and obesity than those in biological and chemical sciences (biology, chemical engineering, pharmaceutical chemistry, and biochemistry). This suggests that though their academic education is linked with health promotion, it is insufficient to change their lifestyles. It underlines the importance of complementary actions to promote the integrative development of health self-care regardless of the students’ academic discipline. Therefore, FES-Zaragoza, UNAM has implemented the University Health Promoter (UHP) model as a policy for integrative professional formation. This constitutes a fundamental strategy for training students in the adoption of healthy lifestyles during their academic development.

The UHP model incorporates health promotion as an educative work project. It has the purpose of promoting human development and improving the QOL of those who study or work. At the same time, it encourages healthy behavior in families, future work environments, and in society in general [20-23].

Among the determining factors for adopting healthy lifestyles, it is necessary to examine gender, socioeconomic level, prior lifestyles, health status, the environment, parental lifestyles and health status, career choice, healthy support networks [24], and overall students’ knowledge about strategies to adopt healthy lifestyles during their time at university. Within this framework, the aim of the present study is to assess the impact of a training program to promote health among university students. Consequently, the trained university students will help create a safe, healthy learning environment at FES-Zaragoza, UNAM, which will in turn promote the development of an integrative health culture. At the same time, healthy lifestyles in terms of self-care will be promoted in the student community.

## Methods

After receiving signed informed consent from the students for participation, we will carry out a randomized trial using a sample of 280 new undergraduate students at FES-Zaragoza, UNAM. The groups will be as follows. (i) An experimental group (n = 140) of 20 students will be made up from each of the seven departments (careers); these participants will receive training as “university student health promoters” through an e-learning course, in which the topics established for a UHP will be reviewed [21,22] (Table 1). (ii) The control group (n = 140) will consist of 20 students from each of the seven departments (careers), but they will undergo no training (Figure 1).

**Table 1 T1:** E-learning topics for the training of university health promoters

-My virtual classroom	-Body hygiene and health
-University student health determinants	-Safe and healthy environment
-How does my body work	-Addiction prevention
-Communication for health	-Conflict management
-Student leadership and health	-Recreation and health
-Health promotion: university health promoter	-Health and cultural activities
-Self-care	-Student support networks and health self-monitoring
-Healthy eating	-First Aid
-Physical activity and health	-University tutoring for health
-Self-esteem and health	-Ethics and health self-care

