### Sample size

For the calculation of sample size it was assumed a prevalence of 40% of overweight and obesity considering the results of the unpublished studies. We considered a significance level of 5%, a difference in clinical interest of 10% related to the control group, and a precision of 2.5% with a power of the 90%.

A healthy-lifestyle questionnaire will be given to all the participants, and the parameters will be detailed in the self-care card before and after the training (Additional file 1: Table S2 and Additional file 2: Table S3). The study variables will be as follows: (i) independent variable—compliance with the e-learning course for promoting health; (ii) dependent variables—lifestyles changes prior to the educative intervention (including healthy eating, physical activity, and addiction prevention) and parameters related to health status in self-care (including weight, body mass index, waist circumference, and hip circumference); and (iii) intervenient variables—age, gender, health status before training, current lifestyle (before training), family income, academic course, parents’ schooling, and parents’ health status. All dependent variables will be measured prior to and after the educative intervention.

Later, the students who comply satisfactorily with the e-learning course will replicate the course to 10 of their classmates. We are considering a follow-up every 6 and 12 months during 4 years.

Data will be processed using SPSS ver. 15.0 (SPSS, Inc., Chicago, IL, USA) statistical software. Descriptive statistics will be presented as means ± standard deviations. Results will be analyzed using Student’s *t* test and logistic regression analysis odds ratios with 95% confidence intervals. Pearson’s correlations will be obtained and *p* <0.05 will be considered significant. Analysis of the open answers will be conducted using ATLAS. ti 5.5 software.

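### Arms are matched 20 to 20 in each of seven careers, but the named Student's t test uses neither career nor the pre-training value; the loss from career alone is small and the remedy nearly free

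*Protocol article*

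**What the plan says.** **Design (Methods).** The protocol article states that "we will carry out a randomized trial using a sample of 280 new undergraduate students". The arms are then set by career: for the experimental arm (n = 140), "20 students will be made up from each of the seven departments (careers"), and "The control group (n = 140) will consist of 20 students from each of the seven departments (careers"). Career is therefore equally represented in the two arms at enrolment. The article does not say in words that randomisation is done within career, but the fixed 20/20 quota has the same effect on balance.

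**Career as a prognostic factor (Background).** Students in the four health-science careers "had a higher percentage of overweight and obesity than those in biological and chemical sciences". The determinants of healthy lifestyle that the authors want examined include "parental lifestyles and health status, career choice, healthy support networks". A direction is given for overweight and obesity; no size is given.

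**Analysis (last paragraph of the Sample size section).** "Results will be analyzed using Student’s *t* test and logistic regression analysis odds ratios with 95% confidence intervals". No career term or stratification is attached to either method. Career appears once in that section, in the list of intervenient variables: "family income, academic course, parents’ schooling, and parents’ health status". The article does not say how the listed variables are used. The dependent variables are all measured before and after the training.

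**The concern.** When a factor is balanced between arms by design, its variation cancels from the difference between the arm means. A two-sample t test does not know this and leaves the variation in its error term. The standard error is then larger than the true sampling variability of the difference, intervals are a little too wide, and some power is lost. The same test also leaves the pre-training measurement unused.

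The article balances the arms on career and describes career as related to the outcome domain. It then names, for outcomes such as weight, body mass index and girths, a test that can take no covariate. What is at stake is precision. The arm difference itself is not biased by this, and the error runs in the conservative direction.

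**Working it through.** **1. The layout reproduces.** 7 careers × 20 = 140 per arm; 2 × 140 = 280 in total, as stated.

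**2. Formula.** Let r be the share of outcome variance that lies between careers. With exact balance, the variance of the arm difference contains only the within-career part, a fraction 1−r of the total. The t test estimates its standard error (SE) from the whole. Hence:

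- t-test SE / true SE ≈ 1/√(1−r)
- true type I error of the nominal 5% test ≈ 2 × [1 − Φ(1.96/√(1−r))]

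**3. A range for r (assumption).** The documents give no value. Take the 40% overall prevalence from the Sample size section, so the total variance is 0.4 × 0.6 = 0.24. Let four health careers and three other careers, equally represented, differ by a gap d. The between-career variance is (4/7)(3/7)d² = (12/49)d², so r = (12/49)d²/0.24.

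| Assumed gap d | r | SE too large by | Type I error |
|---|---|---|---|
| 5 points | 0.0026 | 0.13% | 5.0% |
| 10 points | 0.0102 | 0.51% | 4.9% |
| 15 points | 0.0230 | 1.17% | 4.7% |
| 20 points | 0.0408 | 2.11% | 4.5% |

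Applying these shares to weight, body mass index or girths is a further assumption, because the Background speaks only of overweight and obesity. The split also ignores any differences among careers within the two groups.

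**4. What larger shares would need.** Solving for d gives d = √(r × 0.24 × 49/12). For r = 0.05, d = √0.049 = 0.22; for r = 0.10, d = √0.098 = 0.31. These are gaps of about 22 and 31 points.

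**5. Simulation check.** Seven careers × 20 per arm, outcome SD 1, 10,000 runs per setting. Power is at a difference of 0.3349 SD.

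| r | Mean SE: t test / career-adjusted | Type I error: t test / adjusted | Power: t test / adjusted |
|---|---|---|---|
| 0 | 0.1193 / 0.1193 | 5.1% / 5.1% | 80.3% / 80.3% |
| 0.02 | 0.1194 / 0.1182 | 4.7% / 5.0% | 80.1% / 80.5% |
| 0.05 | 0.1194 / 0.1164 | 4.4% / 4.9% | 80.1% / 81.5% |

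The simulation agrees with the formula. At r = 0.02, 0.1194/0.1182 = 1.010, and 1/√0.98 = 1.010.

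**6. Cost in degrees of freedom.** The t test has 280 − 2 = 278. Career adds 6 parameters and the pre-training value adds 1, leaving 271.

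**The case against.** - **The form of the t test is not stated.** The article does not say that it is two-sample, that it compares arms, or that it is applied to post-training values. A paired test within arm, or a t test on change scores, fits the text as well. A stable difference in level between careers then cancels, and most of the loss described here goes with it. This stands, and the conclusion is conditional on it.
- **Career is not forgotten.** It is a listed intervenient variable, logistic regression can take covariates, and the only evidence of a career difference concerns a binary outcome. A reader might infer that the plan ignores career altogether. The text does not support that; the logistic model may well include it. This answer does not reach the t test, which cannot take a covariate.
- **Covariate detail may sit in an analysis plan that is not shown.** That is fair for detail. But the article does name the test, and it is that named test which does not use the design.
- **The declared independent variable is compliance with the course, not arm.** A comparison by compliance would not keep career at 20 v 20, and the balance argument would not apply. The argument here concerns the comparison of randomised arms.
- **Balance holds at enrolment only.** Follow-up over four years is being considered, and losses would disturb it. That weakens the exact formula, but it is no argument for leaving career out of the model.
- **The baseline value may matter more than career.** It would be expected to absorb much of what career explains. This is likely, and it is a reason to include both. The gain from baseline is not quantified here, because the documents give no before-after correlation.

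**Conclusion.** The point holds as a modest loss of precision. If the t test compares the arms on post-training values, its standard error is about 0.1% to 2% too large for assumed prevalence gaps of 5 to 20 points. Type I error is then about 4.5% to 5.0%, and the loss of power is small: 0.4 percentage points in the simulation at r = 0.02. On change scores the loss is smaller still. The result rests on three assumptions: the value of r, the carry-over from overweight prevalence to the continuous outcomes, and intact 20/20 balance.

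Two stronger readings are tempting. A reader might infer that the plan's intervals are materially wrong; the direction is conservative, the arm difference is not biased by the omission, and the size is of the order of 1%. A reader might also infer that ignoring career throws away about a tenth of the sample. That would need r = 0.10, equivalent to an overweight gap of about 31 points between health and other careers, and nothing in the documents supports such a gap. The case for acting is that the better analysis uses data already collected and costs almost nothing.

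**What to change.** In the analysis paragraph of the Sample size section:

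1. For the between-arm comparison of continuous outcomes, replace the t test with a linear model containing randomised arm, career (7 levels) and the pre-training value of the same outcome. Report the adjusted arm difference with its 95% confidence interval.
2. State that career, already listed among the intervenient variables, enters the logistic model for overweight/obesity together with randomised arm, and that the resulting odds ratio is conditional on career.
3. If a t test is kept for another purpose, such as before-after change within an arm, say so.

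The cost is a wording change and 7 degrees of freedom out of 278. No new data are needed, since career and the pre-training values are already to be recorded. The gain from career alone should be described as modest.

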**Figure 1 F1:**
[figure not shown]
General scheme.

### Sample size

For the calculation of sample size it was assumed a prevalence of 40% of overweight and obesity considering the results of the unpublished studies. We considered a significance level of 5%, a difference in clinical interest of 10% related to the control group, and a precision of 2.5% with a power of the 90%.

A healthy-lifestyle questionnaire will be given to all the participants, and the parameters will be detailed in the self-care card before and after the training (Additional file 1: Table S2 and Additional file 2: Table S3). The study variables will be as follows: (i) independent variable—compliance with the e-learning course for promoting health; (ii) dependent variables—lifestyles changes prior to the educative intervention (including healthy eating, physical activity, and addiction prevention) and parameters related to health status in self-care (including weight, body mass index, waist circumference, and hip circumference); and (iii) intervenient variables—age, gender, health status before training, current lifestyle (before training), family income, academic course, parents’ schooling, and parents’ health status. All dependent variables will be measured prior to and after the educative intervention.

Later, the students who comply satisfactorily with the e-learning course will replicate the course to 10 of their classmates. We are considering a follow-up every 6 and 12 months during 4 years.

Data will be processed using SPSS ver. 15.0 (SPSS, Inc., Chicago, IL, USA) statistical software. Descriptive statistics will be presented as means ± standard deviations. Results will be analyzed using Student’s *t* test and logistic regression analysis odds ratios with 95% confidence intervals. Pearson’s correlations will be obtained and *p* <0.05 will be considered significant. Analysis of the open answers will be conducted using ATLAS. ti 5.5 software.

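### The trial is sized on overweight/obesity prevalence, which is neither named as an outcome nor tied to a test, and 280 students do not give it the stated 90% power

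*Protocol article*

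**What the plan says.** All of this is in the Methods of the protocol article, mostly under Sample size.

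- **Sizing.** "For the calculation of sample size it was assumed a prevalence of 40% of overweight and obesity". The text continues with "We considered a significance level of 5" per cent, "a difference in clinical interest of 10% related to the control group", a precision of 2.5% and a power of 90%. It does not say whether the test is one- or two-sided, or whether the 10% is absolute or relative.
- **Numbers.** "we will carry out a randomized trial using a sample of 280 new undergraduate students at FES-Zaragoza, UNAM", that is, 140 per arm with 20 students from each of seven departments.
- **Dependent variables.** There are two groups. The lifestyle group is worded as "lifestyles changes prior to the educative intervention (including healthy eating, physical activity, and addiction prevention"). The body-measurement group, which comes next, is worded as "parameters related to health status in self-care (including weight, body mass index, waist circumference, and hip circumference"). The Abstract gives the same two groups. A later sentence under Sample size says that all dependent variables are measured both before and after the course.
- **Tests.** Student's t test and logistic regression with odds ratios and 95% confidence intervals. Neither is assigned to a particular outcome.

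**The concern.** The sizing paragraph describes a binary outcome, overweight or obese. The outcome list that follows names lifestyle changes and four body measurements but not that status, and nothing says which listed variable answers the question the trial was sized for. No listed outcome therefore has a stated power, and the outcome with a stated power is not listed. With several outcomes and two tests to choose from, the main result could be picked after the data are seen.

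The stated power is also too high for the prevalence comparison itself. A null result would be read as coming from a trial with a 10% chance of missing the effect, when the chance of missing it is more than half on a two-sided test.

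**Working it through.** **Inputs from the article:** 140 per arm; control prevalence 0.40; difference 10%; significance 5%; power 90%. **Assumptions:** the difference is taken first as absolute (0.40 against 0.30), the test as two-sided, and all 280 students as analysed. Alternatives are shown.

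**1. Can 280 be reproduced?** Two-proportion formula with pooled variance under the null:

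n per arm = [z₁₋α/₂ √(2p̄(1−p̄)) + z₁₋β √(p₁(1−p₁)+p₂(1−p₂))]² / (p₁−p₂)²

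With p̄ = 0.35: [1.960 × √0.455 + 1.2816 × √0.45]² / 0.01 = [1.3221 + 0.8597]² / 0.01 ≈ 476.01, rounded up to **477 per arm, 954 in total**.

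| Reading of the 10% | n per arm for 90%, two-sided | n per arm for 90%, one-sided | Power at 140 per arm, two-sided | Power at 140 per arm, one-sided |
|---|---|---|---|---|
| 40% v 30% | 477 | 388 | 42% | 54% |
| 40% v 50% | 519 | 423 | 39% | 51% |
| 40% v 36% (relative) | 3093 | 2521 | 10% | 17% |

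No two-arm reading at 90% power gives 140 per arm. Reading the 2.5% as the precision of a single prevalence gives 1.96² × 0.24 / 0.025² ≈ 1475. The near matches all need 80% power and a one-sided test: 281 per arm (so 562 in total) from the two-sample formula, or 142 from a one-sample formula. The article states 90%.

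**2. Power for the sized outcome at 140 per arm.** Φ{[√140 × 0.10 − 1.3221] / √0.45} = Φ{(1.1832 − 1.3221) / 0.6708} = Φ(−0.207) = **42%**. One-sided, 1.3221 becomes 1.645 × 0.6745 = 1.1095, which gives Φ(0.110) = 54%. The difference detectable with 90% power is about 18 points two-sided or 16 one-sided.

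**3. The same effect on BMI, a listed outcome.** Assume BMI is normal and every student shifts equally. Moving the proportion above a fixed cut-off from 40% to 30% is a shift of z₀.₇₀ − z₀.₆₀ = 0.5244 − 0.2533 = 0.271 SD, whatever the SD.

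Unadjusted t test (normal approximation): 0.271 × √(140/2) = 2.268, and Φ(2.268 − 1.960) = **62%**. Power of 90% needs √(2/140) × (1.960 + 1.2816) = 0.39 SD.

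**4. BMI adjusted for baseline BMI.** Adjustment multiplies the residual SD by √(1−r²), where r is the correlation between baseline and follow-up BMI. The article gives no r, so a range is shown.

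| r (assumed) | √(1−r²) | 2.268 / √(1−r²) | Power at 280 |
|---|---|---|---|
| 0.6 | 0.800 | 2.835 | 81% |
| 0.7 | 0.714 | 3.176 | 89% |
| 0.8 | 0.600 | 3.780 | 97% |
| 0.9 | 0.436 | 5.203 | over 99% |

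Power reaches 90% when √(1−r²) = 0.271 / 0.387 = 0.70, that is, at r of about 0.71.

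**The case against.** **The outcome is not really missing.** BMI is listed, the list is open-ended, overweight/obesity follows directly from BMI, and logistic regression suits a binary outcome. This stands. A reader might infer that the sized question is absent and can never be tested, or that the listed outcomes are meant mainly for the t test. The text supports neither. The outcome is obtainable but undeclared, and the two tests are listed without ranking. A formal outcome hierarchy may also sit in a fuller protocol or analysis plan. However, the article itself prints a sizing outcome and an outcome list that do not meet, and a power that its own inputs contradict.

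**The 42% does not measure the mismatch.** This also stands. The 42% is for the very outcome used in the sizing, so it reflects faulty sizing arithmetic. Under the model above, the listed BMI outcome has more power than the sized one. The mismatch and the arithmetic are two separate defects.

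**The BMI figures rest on a model.** They do. If the course acts mainly on heavier students, the shift is not uniform and the comparison between prevalence and mean BMI could change. The 42% needs no such assumption.

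**The wording of the lifestyle outcome.** Read literally, "lifestyles changes prior to the educative intervention (including healthy eating, physical activity, and addiction prevention") places the change before the course, and a reader might conclude that the outcome is one the course cannot affect. The later sentence on measurement before and after shows the intent. It is a slip and has no bearing on the sample size.

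**Conclusion.** The point holds with limited scope. The trial is sized on overweight/obesity prevalence, but that status is not named among the dependent variables in either list and no planned test is linked to it. The stated 90% power is not delivered. For 40% against 30% at 140 per arm it is about 42% two-sided or 54% one-sided, and 90% needs about 477 per arm. If the 10% is relative, two-sided power is about 10%. An unadjusted t test on BMI for the equivalent shift does not reach 90% either, at about 62%.

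The prevalence figures rest on the article's inputs, with the readings of the 10% and the sidedness shown. The BMI figures also assume normality, a uniform shift and, for the adjusted analysis, a baseline correlation that the article does not give. No dropout is allowed for, and any loss would lower every power figure.

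**What to change.** Name one outcome that links the sizing to the analysis.

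- **Preferred:** BMI after the course, compared by randomised group and adjusted for baseline BMI. Restate the sizing on this outcome, giving the assumed shift, SD and baseline correlation with their source. For the 0.27 SD shift, 280 students are enough for 90% power if the correlation is about 0.71 or higher.
- **If prevalence is kept:** list overweight/obesity status, derived from BMI, as a dependent variable and assign it a test. Replace the 90% claim with about 42% power for 40% against 30%, or with a detectable difference of about 18 points at 90% power. Naming the outcome while leaving the 90% in place would not be enough, and keeping 90% for a 10-point difference would take about 954 students.

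In either case the sponsor should fix the time point and state whether the test is two-sided and whether the 10% is absolute.

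As a separate editorial correction, reword the lifestyle outcome in the Abstract and under Sample size so that it refers to change from before to after the educative intervention.

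The cost is rewording in two places and one recalculation. BMI is already measured before and after the course, so no new data are needed. The price is committing to one outcome and one time point in advance and, if prevalence is kept at 280, admitting the low power.
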